### Definition of sepsis-associated immunosuppression

We will define ‘sepsis-associated immunosuppression’ as two or more abnormalities (from low HLA-DR, low CD88, raised PD-1 or raised percentage regulatory T cells) that persist for 3 or more days.^14 26^ Previous reports have shown that the persistence of immune dysfunctions is associated with worse clinical outcome, including increased hospital-acquired infections and death.^10 13 15^ The ‘non-immunosuppressed’ group will be patients who do not meet these criteria.

### Sample size

The sample size is based on detection of a difference in antibiotic durations between the ‘sepsis-associated immunosuppression’ and ‘non-immunosuppressed’ groups. The 2016 Surviving Sepsis Campaign guidelines recommended 7–10 days of antibiotics for patients with sepsis.^27^ We have assumed that patients with sepsis-associated immunosuppression will have longer durations (10 days) and so with a SD of 6 days (derived from the ADAPT-sepsis trial), then a sample of 180 patients is required to detect a difference of 3 days in antibiotic treatment between the ‘sepsis-associated immunosuppressed’ and ‘non-immunosuppressed’ patients with 90% power, a 5% alpha and a 5% withdrawal rate.

### Data analysis plan

A formal analysis plan will be finalised and deposited on an open access platform before the database is locked.

For the primary objective, the time it takes for antibiotics to be stopped in patients during the ADAPT-sepsis biomarker-guided antibiotic phase will be summarised and the distribution of the outcome described for the ‘sepsis-associated immunosuppression’ and the ‘non-immunosuppressed’ groups. The mean number of antibiotic days will be compared between groups obtained from linear regression models and adjusted for confounding variables. In addition, each of the cellular markers will be assessed as a continuous outcome. The change in cellular markers between each time point will be correlated with the number of days on antibiotics using Spearman’s correlation coefficient. One sample t tests will be used to assess the changes between time points.

The trial outcomes of 28-day antibiotics, hospital-acquired infections and length of ICU-stay and hospital-stay will be summarised for the ‘sepsis-associated immunosuppressed’ and ‘non-immunosuppressed’ groups. Differences between groups will be assessed using linear regression for continuous variables and logistic regression for categorical variables. We will describe the difference between the groups using p values, point estimates and 95% CIs.

For the secondary objective, we will assess the difference in the PCT/CRP levels and cellular markers for patients who met the criteria for ‘sepsis-associated immunosuppressed’ and when immune profile recovered (ie, became ‘non-immunosuppressed’). Assessments will be captured over time, and we will compute a longitudinal analysis (taking time as a random effect) to assess the difference in the two groups.

Subgroup analyses:

Exploratory analysis will be carried out for the following subgroups:

Patients receiving critical care for a medical versus a surgical cause of sepsis;Patients receiving critical care because of trauma versus non-trauma;Patients receiving critical care because of a community-acquired infection versus a hospital-acquired infection;Infection site: community-acquired pneumonia; hospital-acquired pneumonia; urinary tract infection; intra-abdominal infection or positive blood culture;Patients with septic shock, as defined by persistent hypotension requiring vasopressors to maintain an mean arterial pressure (MAP) ≥65 mm Hg and a serum lactate of >2 mmol/L.^1^

Regression models will be used with ‘sepsis-associated immunosuppressed’ as an interaction term by subgroup for number of days on antibiotics.

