## Introduction

Sepsis is a syndrome of life-threatening organ dysfunction secondary to a dysregulated immune response to an infection.^1^ Mortality from sepsis is high, with 31% of patients dying in hospital and a further 15% of survivors dying in the subsequent year.^2 3^ As a leading cause of death, there are an estimated 31.5 million cases of sepsis worldwide each year.^4^ Organ support in a critical care setting is often required and patients with sepsis account for a third of general adult critical care admissions in the UK.^2^

The dysregulated immune response that characterises sepsis is a paradigm of both a pro-inflammatory and an anti-inflammatory response.^5 6^ While these immune states can occur simultaneously, a predominant immunosuppressive profile has been associated with hospital-acquired infections and mortality.^7 8^ While there is no single test for sepsis-associated immunosuppression, well-established leucocyte cell surface markers identify cellular dysfunction and are associated with adverse clinical outcomes. These dysfunctions are demonstrated across both the innate and adaptive immune responses with the most well-established markers being monocyte human leucocyte antigen-DR (mHLA-DR), neutrophil C5a receptor (CD88), percentage of regulator T cells and programmed cell death-1 (PD-1).^9–12^ The persistence of these cellular abnormalities and the accumulation of dysfunctions increase the risk of adverse clinical outcomes.^10 13–15^

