While an immunosuppressive profile has been linked to poor clinical outcomes, the influence that it has in guiding complex clinical decision-making processes, such as those involved in antibiotic stewardship remain uncertain. Antibiotic treatment in sepsis may be life-saving, but the overuse of antibiotics leads to the emergence of antimicrobial resistance (AMR) and adverse clinical outcomes.^16–19^ The optimal duration of antibiotic treatment in sepsis is unknown.^20^ Biomarker-guided antibiotic durations are not recommended for routine use in the UK^21^ and the current evidence for effectiveness is regarded as low quality internationally.^22^ The ADAPT-Sepsis trial (ISRCTN47473244) is a UK National Institute for Health and Care Research (NIHR) Health Technology Assessment-commissioned clinical trial that will evaluate the clinical and cost-effectiveness of procalcitonin (PCT) and C reactive protein (CRP) protocols for biomarker-guided antibiotic duration decisions in a National Health Service setting. This three-arm trial of daily PCT monitoring, daily CRP monitoring or standard of care aims to determine whether the use of these biomarkers reduces total antibiotic use at 28 days (primary superiority outcome), while maintaining treatment safety of 28-day mortality (primary non-inferiority outcome). Investigations into the dynamics of CRP and PCT with mHLA-DR have shown that high levels of CRP or PCT are associated with low expression of mHLA-DR,^23–25^ suggesting CRP and PCT offer a window into the more complex dysregulation of the immune response.

This protocol outlines a mechanistic study embedded within the ADAPT-Sepsis trial. RISC-sepsis will immune phenotype patients using leucocyte surface biomarkers and dichotomise patients into two groups, ‘sepsis-associated immunosuppression’ and ‘non-immunosuppressed’ (definition below). We will then explore the effectiveness of the biomarker-guided antibiotic duration intervention and the impact on trial outcomes for patients with sepsis-associated immunosuppression.

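### Antibiotic days and lengths of stay are compared as raw days with no account of death, and 28-day mortality is not among the outcomes compared; the resulting bias can go in either direction

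*Protocol article*

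**What the plan says.** All references are to the protocol article.

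- **Model for the main comparison** (Data analysis plan): "The mean number of antibiotic days will be compared between groups obtained from linear regression models and adjusted for confounding variables".
- **Other compared outcomes** (same section): "The trial outcomes of 28-day antibiotics, hospital-acquired infections and length of ICU-stay and hospital-stay will be summarised for the" two phenotype groups. Continuous outcomes are assigned to linear regression and categorical ones to logistic regression. Mortality is not named here, nor in the Outcomes section.
- **Parent trial** (Introduction): it asks whether biomarker guidance "reduces total antibiotic use at 28 days (primary superiority outcome), while maintaining treatment safety of 28-day mortality (primary non-inferiority outcome").
- **Death rate** (Introduction): "Mortality from sepsis is high, with 31% of patients dying in hospital". The Introduction and the definition of the phenotype both associate immunosuppression with death.
- **Primary objective:** differences in the parent trial's outcomes between the two phenotype groups.
- **Exposure definition:** at least two abnormalities lasting 3 days or longer. Everyone else is non-immunosuppressed.
- **Sample size:** "The sample size is based on detection of a difference in antibiotic durations between the" two groups; "a sample of 180 patients is required to detect a difference of 3 days in antibiotic treatment", "with a SD of 6 days (derived from the ADAPT-sepsis trial"), "with 90% power, a 5% alpha and a 5% withdrawal rate".

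**The concern.** Death ends an antibiotic course, an ICU stay and a hospital stay. A linear model of raw days cannot tell a patient who stopped antibiotics safely on day 5 from one who died on day 5. Adjusting for baseline confounders does not help, because death happens after baseline. The problem is not marginal here: by the article's own account death is common and is associated with the exposure being compared.

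The missing mortality comparison makes this worse. The parent trial pairs antibiotic use with 28-day mortality as its safety outcome. This substudy sets out to compare the parent trial's outcomes by phenotype, but names only the antibiotic side and the stays. Without mortality beside them, a reader could not tell whether a shorter course reflects recovery or early death.

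The exposure definition adds a second mechanism. A patient must survive long enough to show persistence, so one who dies very early cannot be classed as immunosuppressed and falls by default into the comparator with a very short course.

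**Working it through.** **Step 1. The plan's own sample size.** Difference 3 days, SD 6, 90% power, 5% alpha (two-sided assumed), equal groups (assumed; the article does not give the prevalence of the phenotype).

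n per group = 2 × (1.960 + 1.282)² × 6² / 3² = 2 × 10.51 × 4 = 84.1, so 85. Total 170; 170 / 0.95 = 178.9, so 179. A t-test calculation needs 86 per group: 172 / 0.95 = 181.1, so 182. The stated 180 is reproduced and is not in dispute.

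**Step 2. Inputs for the illustration.** From the article: 10 days in the immunosuppressed group, 7 in the other, SD 6. Assumed, because the article gives neither mortality by group nor timing of death: gamma-distributed courses; 28-day mortality 40% versus 25%, or 45% versus 20%; and either a constant death hazard over 28 days or early deaths (exponential, mean 8 days among those who die).

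For a gamma course with shape k and scale θ, cut by an exponential death time with mean m:

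mean observed days = m × {1 − (1 + θ/m)^(−k)}

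Immunosuppressed: k = (10/6)² = 2.778, θ = 36/10 = 3.6. Comparator: k = (7/6)² = 1.361, θ = 36/7 = 5.143.

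**Step 3. Deaths stay in their own group.**

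- Early deaths, m = 8: those who die average 8 × (1 − 1.45^−2.778) = 5.15 days in the immunosuppressed group and 8 × (1 − 1.643^−1.361) = 3.93 in the other.
  - 40% v 25%: (0.60 × 10 + 0.40 × 5.15) − (0.75 × 7 + 0.25 × 3.93) = 8.06 − 6.23 = 1.8 days.
  - 45% v 20%: (0.55 × 10 + 0.45 × 5.15) − (0.80 × 7 + 0.20 × 3.93) = 7.82 − 6.39 = 1.4 days.
- Constant hazard, 40% v 25%: m = 28/−ln(0.60) = 54.8 and 28/−ln(0.75) = 97.3. The means are 8.88 and 6.59, a difference of 2.3 days.

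**Step 4. Deaths before day 3 in the immunosuppressed group move to the comparator**, as the persistence rule implies. Take early deaths, 40% v 25%. The share dying before day 3 is 0.40 × (1 − e^(−3/8)) = 0.125. By simulation they have about 1.4 observed days each, so they carry 0.125 × 1.4 = 0.175.

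- Immunosuppressed: (8.06 − 0.175) / 0.875 = 9.01.
- Comparator: (6.23 + 0.175) / 1.125 = 5.69.
- Difference: 3.3 days.

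| Assumed mortality and timing | True difference | Step 3 | Step 4 |
|---|---|---|---|
| 40% v 25%, constant hazard | 3.0 | 2.3 | 3.0 |
| 40% v 25%, early deaths | 3.0 | 1.8 | 3.3 |
| 45% v 20%, early deaths | 3.0 | 1.4 | 3.1 |

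**Step 5. No true difference** (both groups mean 8.5, SD 6; k = 2.007, θ = 4.235; early deaths). Those who die average 8 × (1 − 1.529^−2.007) = 4.59 days.

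- 45% v 20%, deaths left in place: (0.55 × 8.5 + 0.45 × 4.59) − (0.80 × 8.5 + 0.20 × 4.59) = 6.74 − 7.72 = about −1.0 day.
- 40% v 25%, deaths before day 3 moved: the means before moving are 6.94 and 7.52. Then (6.94 − 0.17) / 0.875 − (7.52 + 0.17) / 1.125 = 7.74 − 6.84 = +0.9 days.

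The sign depends on which mechanism dominates.

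**The case against.** **The analysis plan may deal with it.** The article promises a formal plan before database lock, and rules for deaths are often placed there. No sentence says that a death counts as a completed course; that follows from modelling raw days with no stated rule. The Outcomes list is also introduced as inclusive rather than closed. This limits the point but does not remove it: the article fixes the linear model, and its own list of compared outcomes omits mortality.

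**A reader might infer that the plan will mask, or even reverse, the hypothesised longer course in the immunosuppressed group.** The article does not support that. No scenario above reverses a true 3-day difference. Once the persistence rule is applied, the shrinkage disappears or turns into slight inflation. With no true difference, the spurious result can favour either group.

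**A reader might also infer that the study is underpowered.** That does not follow either. The 180 reproduces. Holding the SD at 6 with 86 and 85 evaluable patients, power in the Step 3 scenarios is about 70%, 51% and 34%. In the Step 4 scenarios, with the simulated SD, it is 93-97%. The SD of 6 comes from the parent trial and may already include patients who died; the article does not say that 10 and 7 days are death-free courses.

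**The study is exploratory and sized on mean days.** This stands as a reason not to displace the mean-days comparison as the lead analysis.

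**Conclusion.** The point holds as a problem of interpretation with uncertain direction. The plan compares antibiotic days and stays as if death were a short course or stay. It leaves out the one parent-trial outcome that would show whether this matters, despite a primary objective that covers the parent trial's outcomes.

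Under the assumed mortality, a true 3-day difference could appear as anything from about 1.4 to 3.3 days, and a null difference as about −1.0 to +0.9 days. These ranges rest on assumed group mortality, assumed timing of death, gamma-distributed courses and equal groups. They show how far the estimate can move; they do not predict the result. The mortality omission and the linear model are read directly from the article and need no assumption.

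**What to change.** Before database lock:

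1. Add 28-day mortality to the outcomes compared between phenotype groups, by logistic regression with the same covariates.
2. Keep the mean-days linear regression, on which the study is sized, and state how patients who die are counted in it.
3. Report beside it an analysis that handles death explicitly. Either treat antibiotics stopped while alive, and discharge alive from ICU and hospital, as events with death competing; or use days alive and free of antibiotics or hospital.
4. Start that analysis from a landmark at the time the phenotype can be classified, so that survival to classification does not drive the result. State how many patients die before the landmark.

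Cost: wording in the analysis plan and some extra analysis. Clinical outcome data already come from the parent trial, which has 28-day mortality as a primary outcome, so no new collection should be needed. The added estimate is not a simple mean difference in days, and the landmark analysis loses patients whose event comes before it.

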### Hypothesis

Sepsis-associated immunosuppression will be associated with longer duration of antibiotics, due to persistently raised PCT and CRP; more hospital-acquired infection and more antibiotic treatment days.

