### Outcomes

The primary outcomes are markers of blood leucocyte function measured by flow cytometry. These primary markers are:

Monocyte HLA-DRNeutrophil CD88PD-1 on T lymphocytes (CD4-positive and CD8-positive), monocytes and neutrophilsPercentage of regulatory T cells

Secondary outcome measures include outcome measures derived from the ADAPT-Sepsis trial including duration of antibiotics during the ADAPT-Sepsis intervention phase; total antibiotic days measured at 28 days; occurrence of hospital-acquired infection and length of ICU-stay and hospital-stay. Secondary measures will also include PCT and CRP concentrations in serum.

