### Sampling and data collection

As a substudy within the ADAPT-Sepsis trial, all RISC-sepsis procedures and sampling will occur within the trial. Sampling will occur during the ADAPT-Sepsis intervention period when blood is sampled daily. While additional blood samples are taken from patients for RISC-sepsis, there is no increase in number of sampling episodes. Patients will have blood sampled on alternate days up to four sampling points (days 1, 3, 5 and 7). Blood for flow cytometric analysis will be collected in Cyto-Chex (Streck, La Vista, USA) blood preservation tubes before shipping to a central testing hub (Newcastle University). Serum will be collected, frozen and stored at site until the end of the recruitment period.

Baseline clinical data and outcome data will be obtained from the ADAPT-sepsis data collection. Baseline data will include admission diagnosis, site of infection, acute physiology and chronic health evaluation (APACHE) II and sequential organ failure assessment scores and sepsis bundle care elements in the first 24 hours. In addition, at each RISC-sepsis sampling point, the circulating white cell count and differential count will be recorded.

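### Hospital-acquired infection is to be compared by logistic regression on occurrence, although the phenotype is only established after enrolment; time order and time at risk are unprotected, and both biases favour the hypothesis

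*Protocol article*

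**What the plan says.** All references are to the protocol article.

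- **Outcome.** The Outcomes section lists, among measures taken from the parent trial, "occurrence of hospital-acquired infection and length of ICU-stay and hospital-stay". It gives no start day, end day or person-time.
- **Comparison.** The Data analysis plan states: "The trial outcomes of 28-day antibiotics, hospital-acquired infections and length of ICU-stay and hospital-stay will be summarised" for the two phenotype groups. It continues: "Differences between groups will be assessed using linear regression for continuous variables and logistic regression for categorical variables". Results are to be given as p values, point estimates and 95% CIs.
- **Exposure.** The Definition section requires two or more abnormalities "that persist for 3 or more days". The Sampling section supplies the measurements: "Patients will have blood sampled on alternate days up to four sampling points (days 1, 3, 5 and 7".
- **Reference group.** "The ‘non-immunosuppressed’ group will be patients who do not meet these criteria". No exception is stated for patients who die, leave or stop being sampled too early to be classified.
- **Direction expected.** The Hypothesis section expects immunosuppression to go with "more hospital-acquired infection and more antibiotic treatment days".

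The Data analysis plan also says that a formal analysis plan will be finalised before database lock. That plan is not shown.

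**The concern.** Three stated choices combine badly: an exposure that takes days of follow-up to establish, a reference group made up of everyone else, and a model for bare occurrence.

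1. **Time order.** The phenotype can be established as late as day 7. An infection on day 4 may precede, and may contribute to, abnormal markers on days 5 and 7. Nothing in the article prevents it from being analysed as a consequence of the phenotype.
2. **Time at risk.** A patient who dies or is discharged before persistence can be shown can only be classed as non-immunosuppressed, and has had little time to acquire an infection. An immunosuppressed patient has by definition stayed long enough to be classified. Logistic regression on occurrence uses no person-time and does not treat death or discharge as competing events.

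Both push the estimate towards the hypothesis. The confounder adjustment in the Data analysis plan is stated for antibiotic days. Extending it to infection would not help, because baseline covariates correct neither problem. Infection is labelled secondary, but the primary objective is the difference in trial outcomes between these two groups, and infection is one of three hypothesised effects.

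**Working it through.** **The plan's own figure.** The article gives no figure for infection. Its sample size concerns antibiotic days: difference 3, SD 6, 90% power, 5% alpha (taken as two-sided), 5% withdrawal. Per group, 2 × (1.960 + 1.282)² × 6² / 3² = 84.1, rounded up to 85. The total is 170, and 170 / 0.95 = 179. The stated 180 reproduces and is not affected by this point. After withdrawal, 180 × 0.95 = 171 patients remain for analysis.

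**Assumptions, none from the documents.** Daily infection hazard h of 0.01, 0.02 or 0.03. Daily hazard e of leaving hospital, dead or alive, of 0.03, 0.06 or 0.10. Infections counted to day 28. Half of patients would show the phenotype if observed long enough. The phenotype needs presence to day 5. The true odds ratio is 1.

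**Time at risk alone, middle case (h = 0.02, e = 0.06).**
- Present to day 5: exp(−4 × 0.06) = 0.787, so 0.213 leave earlier.
- A patient leaving on day k has an infection with probability 1 − exp(−0.02k). Averaged over exit days, this is 4.7% in those leaving before day 5 and 28.0% in those who stay.
- Immunosuppressed: half of the stayers (0.393 of all patients), 28.0% infected.
- Non-immunosuppressed: the other half of the stayers plus all early leavers, (0.393 × 0.280 + 0.213 × 0.047) / (0.393 + 0.213) = 0.198.
- Odds ratio: (0.280/0.720) / (0.198/0.802) = 1.57, with no true effect.

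**Full grid.** A null simulation with 2,000,000 patients per scenario gave:

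| Scenario | Infected, immunosuppressed v other | Odds ratio | Rejection at nominal 5%, 171 patients |
|---|---|---|---|
| h 0.01, e 0.03 (lowest) | 19.0% v 15.6% | 1.26 | 9% |
| h 0.02, e 0.06 | 28.0% v 19.7% | 1.58 | 24% |
| h 0.03, e 0.10 (highest) | 31.8% v 19.5% | 1.93 | 44% |

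**If three calendar days suffice.** On that reading, presence to day 3 is enough and the bias shrinks. In the middle case, 1 − exp(−2 × 0.06) = 0.113 leave before day 3 with 2.9% infected, against 25.6% in stayers. The reference group is then (0.443 × 0.256 + 0.113 × 0.029) / (0.443 + 0.113) = 0.210, and the odds ratio is (0.256/0.744) / (0.210/0.790) = 1.29. The same formula over the grid gives about 1.14 to 1.49.

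**Adding reverse order.** With presence to day 5 required, suppose an infection by day 5 raises the probability of the phenotype by 0.2 or 0.4. The odds ratio becomes 1.55 to 2.67 or 1.91 to 3.66. In the simulation, 36% to 61% of all counted infections fell on or before day 7, so the order problem is not confined to a few events.

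**Check of the remedy.** Restricting to patients in hospital and infection-free after day 7 returned odds ratios of 0.99 to 1.02. The number retained is 171 × exp(−7(h + e)), from 171 × exp(−0.28) = 129 down to 171 × exp(−0.91) = 69.

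**The case against.** The strongest reply is that much of this is silence. The outcome comes from the parent trial, whose protocol is not shown, and a formal analysis plan is still to come. A counting window or landmark could properly sit in either. The study is exploratory, infection is a secondary outcome, and the sample size does not rest on it. Eligibility also requires that patients are likely to remain in hospital for 72 hours, so a constant exit hazard may overstate very early discharge. The default into the reference group arises from the phenotype definition and affects other outcomes too.

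Most of this limits the size and priority of the point without removing it. The model, the exposure definition and the default reference group are stated, and followed as written they bias this comparison.

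Three stronger readings are tempting and are not supported:

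- A reader might infer that infections before day 1 count as outcomes. No text says so; a hospital-acquired index infection appears only as a baseline subgroup.
- A reader might infer that infections on days 1 to 7 are definitely counted. The article does not exclude them, which is weaker.
- A reader might compare typical stays. At an infection hazard of 2% per day, 10 v 20 days gives 18.1% v 33.0% (odds ratio 2.2), and 5 v 15 days gives 9.5% v 25.9% (odds ratio 3.3). The arithmetic is right, but the contrasts are assumed and not tied to the mechanism: a patient staying 10 days could have given all four samples. Modelling early exit gives less.

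**Conclusion.** The point stands, as something that should be changed and not as a fatal flaw. The planned comparison protects neither time order nor time at risk, and both biases run towards the hypothesis. With no true effect, time at risk alone gives an odds ratio of about 1.3 to 1.9 if the phenotype needs presence to day 5, and less if day 3 suffices. Larger values need the further assumption that early infection induces the phenotype. Every figure rests on assumed rates, so the direction is firmer than the size. If the parent protocol or the formal plan already restricts counting to infections after classification, the time-order part falls away; the time-at-risk part would remain unless early leavers and competing events are also handled.

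**What to change.** In the formal analysis plan, before database lock:

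1. Make the main analysis of this outcome time to first hospital-acquired infection, with phenotype as a time-dependent exposure that switches on the day persistence is established. Treat death and discharge as competing events through cause-specific hazards. Patients who leave early then contribute only the unexposed time they actually had.
2. Alternatively, use a day-7 landmark: fix the phenotype from samples up to day 7 and count later infections only, in patients in hospital and infection-free at that point. A day-3 landmark would not do while the phenotype can still be established up to day 7, because a day-4 infection followed by abnormal markers on days 5 and 7 would still count.
3. Report infections arising before the phenotype is established descriptively.
4. Keep the logistic model as a sensitivity analysis.

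**Cost.** Analysis wording only, with no new sampling, but infection dates must be available from the parent trial. Fewer events count. The day-7 landmark would keep about 69 to 129 of 171 patients under the assumed rates; the time-dependent model loses less and is preferable for that reason.

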### Rationale

The ADAPT-Sepsis trial will include a heterogeneous population of adult patients with sepsis, including those with sepsis-induced immunosuppression. As a phenotype associated with hospital-acquired infections and reduced infection-free survival, there may be heterogeneity in the effect of the biomarker-guided antibiotic duration intervention for patients with this phenotype. If biomarker-guided antibiotics are ineffective in patients with sepsis-associated immunosuppressed, then a greater degree of patient stratification may be required to ensure optimal antibiotic duration. Furthermore, if CRP and PCT levels fall over the same period that cellular defects resolve, this may give clinicians greater confidence in following biomarker-guided antibiotic durations.

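### The secondary-objective analysis compares markers between states defined by those same markers, and its PCT/CRP contrast cannot separate immune recovery from elapsed time

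*Protocol article*

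**What the plan says.** The section Definition of sepsis-associated immunosuppression sets the rule: "two or more abnormalities (from low HLA-DR, low CD88, raised PD-1 or raised percentage regulatory T cells) that persist for 3 or more days". It then makes the comparison group the complement: "The ‘non-immunosuppressed’ group will be patients who do not meet these criteria". The Introduction likewise splits patients into these two groups.

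Under Data analysis plan, the text for the secondary objective reads "we will assess the difference in the PCT/CRP levels and cellular markers for patients who met the criteria for" immunosuppression "and when immune profile recovered (ie, became ‘non-immunosuppressed". It continues: "we will compute a longitudinal analysis (taking time as a random effect) to assess the difference in the two groups". The Secondary objective section identifies the leucocyte surface markers as the study's primary outcome measures. Under Outcomes these are the same four marker types that define the groups.

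Samples are taken on days 1, 3, 5 and 7. The Rationale says clinicians may gain confidence in biomarker-guided durations "if CRP and PCT levels fall over the same period that cellular defects resolve".

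**The concern.** There are three linked difficulties.

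- **The markers are tested between states built from them.** A visit counts as suppressed because at least two of the four markers are abnormal, and as recovered because that no longer holds. A difference in those markers says little beyond the rule. Selecting patients on crossing a threshold and then watching them cross back also brings in regression to the mean.
- **The PCT/CRP contrast is confounded with time.** A patient can be seen to recover only after being seen to be suppressed. If PCT and CRP fall during treatment for any reason, recovered samples will be lower.
- **One label has two meanings.** 'Non-immunosuppressed' is a class of patients in the definition and a state that a patient can enter in the analysis text. The two groups in the longitudinal model could be either.

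At stake is the interpretation of the secondary objective. Marker differences could be read as biological recovery, and a PCT/CRP difference as evidence that these biomarkers track immune recovery.

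**Working it through.** **The plan's own figure.** The inputs under Sample size are a difference of 3 days, SD 6, power 90%, alpha 5% (two-sided assumed), a 1:1 split (assumed) and 5% withdrawal. Then n per group = 2 × (1.960 + 1.282)² × 6² / 3² = 84.1, so 85; the total is 170, and 170 / 0.95 = 178.9, so 179. A t-test version gives 86 per group and 172 / 0.95 = 181.05, so 182. The stated 180 is reproduced, and nothing below depends on it.

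**Step 1: what the rule fixes in advance.** The natural reading of recovery is that the patient no longer has two abnormalities; the article gives no separate criterion. A suppressed visit then has at least 2 abnormal markers and a recovered visit at most 1. The abnormality count differs by at least 2 − 1 = 1 before any data are seen.

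**Step 2: size with no true recovery.** The simulation used 180 × 0.95 = 171 patients, four visits, four mutually independent markers, no time trend, and only stable patient-level variation plus noise. The documents do not give the following, so they are assumed: 30% or 50% of values abnormal per marker; within-patient correlation 0.3, 0.6 or 0.8; persistence read as two or three consecutive samples. There were 300 runs per scenario. Tests were made only in runs with at least five recovered patients. Ranges are over the two abnormal fractions.

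| Correlation | Samples for persistence | Mean number recovered | Shift per marker (SD) | p<0.05, a single marker | p<0.05, average of four |
|---|---|---|---|---|---|
| 0.3 | 2 | 25-41 | 0.53-0.57 | 74-94% | 100% |
| 0.3 | 3 | 5-14 | 0.53-0.57 | 27-58% | 85-99% |
| 0.6 | 2 | 22-31 | 0.38-0.41 | 61-83% | 99.7-100% |
| 0.6 | 3 | 6-11 | 0.38-0.41 | 22-40% | 76-94% |
| 0.8 | 2 | 18-23 | 0.25-0.26 | 44-58% | 99-100% |
| 0.8 | 3 | 5-8 | 0.26-0.27 | 20-27% | 66-83% |

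A fifth variable outside the definition, standing in for PCT or CRP without a time trend, was significant in the same within-patient contrast in 3-7% of runs, close to the nominal 5%. The inflation comes from testing the defining markers.

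**Step 3: timing of PCT/CRP.** If persistence needs two samples, the earliest sequence is suppressed on days 1 and 3 and recovered on day 5. If it needs three, recovery can be seen only on day 7. Suppose PCT or CRP falls by d SD per visit in everyone, whatever the immune state. With two samples, the suppressed visits average (1 + 2) / 2 = 1.5 and recovery is at visit 3, so the contrast is (3 − 1.5)d = 1.5d. For d = 0.2 to 0.4 (assumed) that is 0.30 to 0.60 SD from elapsed time alone.

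A random effect for time is centred on zero, so it models patients' departures from an average slope and not the average slope itself. If day is absent from the fixed part, the state indicator absorbs part of the common decline. In simulations with d = 0.2-0.4 and no link to recovery, the state effect was falsely significant in about 37-95% of runs with time only as a random effect, against about 2-5% with day as a fixed effect. A smaller set (d = 0.1-0.4, 50 runs per scenario, some convergence warnings) gave 26-98% with a random intercept only, 24-58% with a random slope for time and 2-10% with day fixed. With 50 runs, the standard error of a 5% rate is √(0.05 × 0.95 / 50) = 3 percentage points, so these figures are approximate.

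**Step 4: the label.** In the patient-level split, anyone who has met the criteria is outside the 'non-immunosuppressed' group. In the analysis text the same patient later takes that group's name. The article does not say which use the longitudinal comparison follows.

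**The case against.** The study calls itself exploratory and observational, and its secondary objective is to monitor change. The sentence promising p values and confidence intervals sits in the paragraph on trial outcomes, not in this one. Showing how defining markers move is ordinary characterisation, and 'cellular markers' may include exploratory ones outside the definition, for which nothing is circular. A formal analysis plan is promised before database lock and could settle the recovery criterion and the model. All of this limits the weight of the point. It does not remove it, because the article already states the comparison and how time enters the model.

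Four stronger readings are tempting, and the documents do not support them.

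- **That every marker will be significant by construction.** Only two of four need be abnormal and few patients may recover by day 7; a single marker was significant in 20-94% of runs.
- **That the gap between the patient groups is pure noise.** It is about 0.43-0.66 SD under the assumed correlations but only about 0.26-0.27 SD at zero correlation. Much of it reflects patients whose stable levels really differ.
- **That the 85 per group behind the sample size, with 90% power at 3 / 6 = 0.5 SD, gives the chance of a spurious marker finding.** Those numbers belong to antibiotic duration. The suppressed-to-recovered contrast rests on the recovered patients, about 18-41 or 5-14 in the simulations.
- **That the PCT/CRP analysis cannot serve the Rationale at all.** The Rationale asks whether the changes occur over the same period, and description can answer that.

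**Conclusion.** The point holds for the secondary objective. The direction of the difference in the four defining markers is fixed by the definition, and regression to the mean alone yields about 0.25-0.57 SD per marker. That size depends on assumed abnormal fractions, correlations and independence between markers; the built-in direction does not. The PCT/CRP comparison is not circular, but with time only as a random effect it cannot tell immune recovery from elapsed time. The false-positive rates rest on an assumed common decline and are approximate.

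The double use of 'non-immunosuppressed' is an ambiguity to resolve. A reader might infer that recovered patients change group in the primary analysis, but nothing in the article says so. The sample size and the primary antibiotic-duration comparison stand. The change should be made before the formal analysis plan is finalised.

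**What to change.** 1. Present the trajectories of HLA-DR, CD88, PD-1 and regulatory T cells descriptively by study day, with no test between suppressed and recovered states.
2. Limit between-state inference to PCT, CRP and markers outside the definition, such as PD-L1.
3. In the longitudinal model, include study day as a fixed effect and a patient random effect, so that states are compared at the same day.
4. Define a time-varying state (never met, currently suppressed, recovered) with a stated recovery criterion, and keep it and its labels separate from the patient groups of the primary objective.
5. Report any PCT/CRP result as concurrent change unless the day-adjusted contrast supports more.

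The cost is wording only, with no added patients or samples. Some marker p values are lost, and precision will be limited because few patients may recover by day 7.
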